## **1.2 Trial Rationale and Hypothesis**

There is a current global pandemic of COVID-19 infection. This is caused by a novel virus which was first identified worldwide in December 2019 and has now been detected in every country globally. As of 19th July 2020 there were 294 070 confirmed cases in the UK, and 45 273 deaths since the beginning of 2020. Globally the number of confirmed cases stood at 14 043 611 with 597 583 deaths {World Health, 2020}. As well as this effect on health, it has had major healthcare service, economic and social repercussions. Currently two medications have shown promise for treating severe COVID19: Dexamethasone {The, 2020, Dexamethasone in Hospitalized Patients with Covid-19 — Preliminary Report} and Remdesivir {Beigel, 2020, Remdesivir for the Treatment of Covid-19 - Preliminary Report. Reply}. No medication has yet been proved effective when started early when the disease is still milder. Several IMPs are currently in or about to start testing in clinical trials.

Favipiravir is an antiviral agent that is already used against severe influenza (as outlined in the favipiravir Investigational Brochure) and that has been used in trials against other viruses with promising results. There is therefore a strong rationale for testing favipiravir against COVID-19 and there is an urgent need to do so in a controlled, clinical trial setting.

The working hypothesis for the GETAFIX trial is that favipiravir may be an effective treatment for COVID-19 infection for those patients who have early stage disease, compared to current standard of care. This hypothesis will be tested by evaluating the difference in severity of disease at day 15 as the trial primary endpoint. This study will also provide an important opportunity to evaluate the pharmacokinetic and pharmacodynamic profile of this drug in the context of COVID-19 infection. It is critical to gather this information alongside measures of clinical efficacy, to better understand the clinical outcomes and to provide information for ongoing trials and use of favipiravir. Experimental endpoints will include evaluation of potential mechanisms of resistance of COVID-19 to this drug. If successful at meeting its primary endpoint, the GETAFIX trial has the potential to be highly impactful if favipiravir is considered for use globally to treat COVID-19 to reduce deaths, admissions to hospital and transmission of SARS-CoV-2.

## 2 TRIAL OBJECTIVES

**Table 1: Objectives and Endpoints**

| Primary Objective                                                                                                                                      | Primary Endpoint                                                                                                                                                                                     | Timepoint of assessment                 |
|---------------------------------------------------------------------------------------------------------------------------------------------------------------|-------------------------------------------------------------------------------------------------------------------------------------------------------------------------------------------------------------|------------------------------------------------|
| Assess the efficacy of favipiravir in addition to standard care in patients with COVID-19 in reducing the severity of disease compared to standard care alone | Clinical status as assessed by WHO COVID 10 point ordinal severity scale* at day 15                                                                                                                         | Day 15 (+/- 48 hours)                          |
| Secondary objectives                                                                                                                                   | Secondary Endpoints                                                                                                                                                                                  | Timepoint of assessment                 |
| Assess the effect of favipiravir in addition to standard care in the study population compared to standard care alone                                         | Proportion of patients meeting level 7 or above on the WHO COVID 10 point ordinal severity scale or dead by day 29                                                                                          | Up to and including day 29                     |
|                                                                                                                                                               | WHO COVID 10 point ordinal severity scale level                                                                                                                                                             | Days 8, 29, 60                                 |
|                                                                                                                                                               | Overall survival                                                                                                                                                                                            | Up to and including day 60                     |
|                                                                                                                                                               | Inpatients only:
Viral clearance on or before d8 **                                                                                                                                               | Day 8                                          |
|                                                                                                                                                               | Inpatients only:
Duration of pyrexia in days (defined as a temperature $\geq 38^{\circ}\text{C}$ )                                                                                                | Up to and including day 60                     |
| Evaluate the safety and tolerability of favipiravir in the study population                                                                                   | Adverse events                                                                                                                                                                                              | Up to and including day 60                     |
| Exploratory objectives                                                                                                                                 | Exploratory endpoints                                                                                                                                                                                | Timepoint of assessment                 |
| Evaluate the effect of favipiravir on duration of hospitalisation                                                                                             | Duration of hospitalisation (days)                                                                                                                                                                          | Up to and including day 60                     |
| Understand the pharmacokinetics of favipiravir                                                                                                                | Evaluate the population pharmacokinetics of this dose of favipiravir in the study population and assess the relationship between the pharmacokinetics of favipiravir in the study population and viral load | Please see Appendix 5 for schedule of sampling |

|                                                                                                                            |                                                                                                                              |                                         |
|----------------------------------------------------------------------------------------------------------------------------|------------------------------------------------------------------------------------------------------------------------------|-----------------------------------------|
| Understand the pharmacodynamics of favipiravir                                                                             | Change in viral load with time

Outpatients only:
Viral clearance on or before d8 **                         | Up to and including day 60

Day 8 |
| Understand mechanisms of resistance to favipiravir                                                                         | Sequence of virus in cases of treatment failure                                                                              | Up to and including day 60              |
| Explore the immunological and biometric markers contributing to the clinical condition of patients in the study population | Evaluate the relationship between immunological and biometric markers and the clinical outcomes of the study                 | Up to and including day 60              |
| Post COVID19 health and psycho-social consequences                                                                         | Evaluate the relationship between post COVID-19 health and psycho-social consequences and the clinical outcomes of the study | Up to and including day 60              |

\*See Appendix 1 for WHO COVID-19 10 point ordinal severity scale.

\*\* Defined as a negative SARS-CoV-2 PCR result

### 3 TRIAL DESIGN

GETAFIX is a randomised controlled study of favipiravir as an early treatment arm in COVID-19 patients who are over 16 years old, not pregnant or breastfeeding and without previous co-morbidity. The study is a single-centre, randomized (1:1) open label phase II/III study which allows for early stopping in case of lack of efficacy or clear superiority in the experimental arm. Eligible patients will be randomised between standard care for COVID-19 (Control arm) and standard care plus favipiravir (Experimental arm).

The study is powered to detect an improvement corresponding to an odds ratio of 1.95 in the cumulative odds of the WHO COVID 10-point ordinal severity scale assessed at day 15. This is equivalent to the probability of a patient having a better outcome at this time if allocated to experimental as compared to control of 66% (50% under null hypothesis).

To detect this magnitude of difference with 90% power at the 5% 2-sided level of statistical significance requires 302 patients (151 per arm).

This trial will be performed according to the UK Policy Framework for Health and Social Care (2017) Medicines for Human Use (Clinical Trials) Regulations, 2004 SI 2004:1031 (as amended) and World

### **3.1 Trial population**

In total, 302 adult patients with confirmed COVID-19 by valid COVID-19 test will be recruited to the trial and randomised (1:1) across both the control arm and the experimental arm.

The study population for this trial will include patients aged  $\geq 16$  years old with a confirmed diagnosis of COVID-19, who are not pregnant or breastfeeding. Patients will be entered into this trial within 96 hours of the COVID-19 test being taken. Potentially eligible patients will be identified after community testing, in an acute receiving environment or when admitted to a hospital ward.

### **3.2 Eligibility criteria**

#### **Inclusion criteria**

1. Age 16 or over at time of consent
2. Exhibiting symptoms associated with COVID-19
3. Positive for SARS-CoV-2 on valid COVID-19 test
4. Point 2, 3, or 4 on the WHO COVID-19 ordinal severity scale at time of randomisation. (Symptomatic Independent, Symptomatic assistance needed, Hospitalized, with no oxygen therapy)
5. Have  $\geq 10\%$  risk of death should they be admitted to hospital as defined by the ISARIC4C risk index: <https://isaric4c.net/risk>
6. Able to provide written informed consent
7. Negative pregnancy test (women of childbearing potential\*)
8. Able to swallow oral medication

#### **Exclusion criteria**

1. Renal impairment requiring dialysis or haemofiltration
2. Pregnant or breastfeeding
3. Of child bearing potential\* (women), or with female partners of child bearing potential (men) who do not agree to use adequate contraceptive measures for the duration of the study and for 3 months after the completion of study treatment
4. History of hereditary xanthinuria

5. Xanthine urinary calculi
6. Other patients judged unsuitable by the Principal Investigator or sub-Investigator
7. Known hypersensitivity to favipiravir, its metabolites or any excipients
8. Severe co-morbidities including patients with severe hepatic impairment defined as:
  - greater than Child-Pugh grade A (Appendix 4)
  - AST or ALT > 5 x ULN
  - AST or ALT > 3x ULN and Total Bilirubin >2xULN
9. More than 96 hours since first positive COVID19 test was taken.
10. Unable to discontinue contra-indicated concomitant medications (section 6.7)

\* Non-childbearing potential must be evidenced by fulfilling one of the following criteria at screening:

- Post-menopausal defined as aged more than 50 years and amenorrhoeic for at least 12 months following cessation of all exogenous hormonal treatments.
- Irreversible surgical sterilisation by hysterectomy, bilateral oophorectomy or bilateral salpingectomy but not tubal ligation

**There will be no exception to the eligibility requirements at the time of registration/randomisation. Queries in relation to the eligibility criteria should be addressed via contact with the CTU prior to registration/randomisation. Patients are eligible for the trial if all the inclusion criteria are met and none of the exclusion criteria apply.**

### **3.3 Identification of participants and consent**

Potential participants may be identified before their COVID-19 test result is available and will be randomised within 96 hours of their COVID-19 test being taken. They may be identified either by clinical staff involved in their treatment as per standard of care, or by a clinical member of the GETAFIX trial team. COVID-19 testing centres may provide adverts to attendees who may contact the GETAFIX trial team if interested in participating. Following this, patients will be seen by a clinical member of the GETAFIX trial team who will explain to the patient that they may be potentially eligible for a clinical trial. If the patient is interested in hearing more about the trial, this option will be discussed further with the patient.

After receiving verbal and written information, patients will be given sufficient time to decide whether or not they would like to take part in the trial. All efforts will be made to ensure that patients understand the commitment required to fulfil the trial requirements and facilitate discussion with friends and relatives at the request of the patient. Patients will be told that their

participation is entirely voluntary and that they can leave the trial at any time without their standard care being affected. Patients will then be given the choice of whether they wish to participate. Signed participant consent must be obtained. For patients who have capacity to understand and give consent, but are unable to read the consent form or sign their name, witness consent may be given. The consent forms should also be signed by the person undertaking the consent procedure at site, who must be detailed on the delegation log as having this authorisation. The Principal Investigator is responsible for ensuring the designee is suitably qualified by training or experience to take informed consent, if consent is delegated to a designee.

After the patient has provided informed consent to participate in the trial, the CRUK CTU, Glasgow will provide the site with a screening number for the patient, and screening may commence. No screening activities related to the trial may be undertaken until informed consent has been obtained.

Once the patient has been deemed eligible for the trial by the PI or medically trained designee, 1:1 randomisation into the Control Arm or the Experimental Arm will occur. In order for randomisation to occur, the participating site must fax, telephone or email the CRUK Clinical Trials Unit, Glasgow.

There will be an optional consent form for patients who may want to contribute to more frequent PK and PD sampling. The maximum number of patients who will undergo this testing will be sixteen, eight males and eight females. This option will be offered to all patients who are being treated in hospital at the time of taking informed consent, however only patients in the experimental arm of the trial will be able to undergo this testing.

For those patients who are randomised to the experimental arm of the trial, it is strongly advised that the first dose of favipiravir is administered within 24 hours of the treating clinician receiving a positive SARS-CoV-2 test result.

### **3.4 Registration/Randomisation**

Patients cannot be screened or registered to the trial until the site has been activated to begin recruitment. To register/randomise a patient on the trial, contact the CRUK Clinical Trials Unit, Glasgow. Registration/Randomisation to the trial can be performed by either telephone or fax on the following numbers:

[contact]

[contact]

Email: [[contact]](mailto:[contact])

Registration/Randomisation by telephone or fax will only be available during the following hours:

Mon – Thurs 8.30am – 5pm

Fri 8.30am – 4.30pm

An out of hours service for registering/randomising inpatients will be operational at the following times:

Monday – Thursday from 5.00 pm- 6.00pm

Friday from 4.30pm -6.00pm

Saturday 9am – 4.00pm

Sunday 9am – 12.00pm

**During these times, only randomisations sent by email will be processed.**

**Please check local site Pharmacy opening times – patients should be randomised no later than 1 hour before local site Pharmacy closes.**

**Out of hours randomisation availability is dependent on site Pharmacy and Nursing staff availability – this may differ between sites and at different times according to the progress of the pandemic. Sites will be kept informed of any changes to this service.**

When the patient has consented, a screening number should first be obtained by contacting the CRUK CTU, Glasgow.

When screening is complete and eligibility confirmed, the CRUK CTU Glasgow should be contacted again. The patient's eligibility criteria will be checked and, if eligible, a trial number and trial arm will be allocated at this point.

All patients must be registered/randomised onto the trial prior to commencement of trial treatment.

A minimisation algorithm incorporating a random component will be used to allocate patients to either experimental or control arm. The factors used in the minimisation will be:

- Site
- Age (16 - 50; 51 – 70; 71+)
- History of hypertension or currently obese (BMI>30 or obesity clinically evident) (yes; no)
- <7 days duration of symptoms (yes; no; unknown)
- Sex (male; female).
- WHO COVID ordinal severity score at baseline (2 or 3; 4)

With the patient's consent, their GP will be informed of their involvement in the trial.

### 3.5 Withdrawal

#### 3.5.1 Withdrawal of Patients from Trial Treatment

Patients have the right to withdraw from trial treatment at any point for any reason. Similarly, the investigator may withdraw patients from the trial drug in the event of intra-current illness, AEs, SAEs, SUSARs, protocol violations or any other relevant reasons. **If a patient withdraws from treatment early, they should be followed up as per trial schedule.**

A subject must be discontinued from the trial for any of the following reasons:

- The subject or legal representative withdraws consent
- Patient meets stopping rules criteria (see Section 6.8)
- Investigator's decision to withdraw the subject
- The subject has a confirmed positive serum pregnancy test
- Noncompliance with trial treatment or procedure requirements
- Administrative reasons

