#### 3.5.2 Withdrawal from Trial

In many circumstances where a patient withdraws from trial treatment, it will, nonetheless, be desirable for the patient to remain on the trial (for example for follow-up purposes). If, however, the patient withdraws from the trial itself, it should be clearly documented in the patient's notes what they are withdrawing from (consent to use any past data, consent to use any samples collected or consent for further data collection from the date of consent withdrawal). If a patient withdraws their consent from the trial, the site must contact the CRUK CTU Glasgow with full details of the withdrawal. Where applicable, the CRUK CTU Glasgow may ask the site to complete a Consent

Withdrawal Form to record full details of the consent withdrawal. In the event of withdrawal, data or tissue already collected with consent will be retained and used in the study, but no further tissue will be collected or any other research procedures carried out on or in relation to the participant.

Patients who become unwell to such an extent that they lose capacity during the course of the study will be permitted to continue on IMP until the point they are unable to swallow oral medication, and all other study processes, including safety assessments, should continue. No patient whether they have capacity or not will continue on the trial if it is unsafe to do so in the opinion of the Principal or Chief Investigator, or the Trial Steering Committee.

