### **5.8 Dose Modifications for toxicity**

A subject should be removed from favipiravir treatment if one of the following criteria is met:

- AST or ALT > 5 x ULN
- ALT or AST > 3 x ULN AND total bilirubin > 2X ULN
- AST or ALT > 3 x ULN AND patient has right upper quadrant pain or eosinophilia
- Uric acid >20 mg/dL (1.2 mmol/l)
- Any other ≥ Grade 3 adverse event considered by the study team to be due to the trial drug.

Any > 3 x ULN AST or ALT event should be reported as a AE of Special Interest using the SAE form provided by the CRUK CTU Pharmacovigilance department.

No dose reductions are required for reductions in renal function if they occur during treatment. There no data for treatment with favipiravir during haemofiltration or dialysis – if this occurs during treatment the Sponsor & CI should be contacted to discuss the risk-benefit of continuing treatment for the individual case.

If remdesivir is administered in combination with favipiravir, EGFR must be >30ml/min and LFTs must be monitored daily during treatment with remdesivir. The stopping rules above for raised

transaminases apply for the combination treatment. Ensure remdesivir SmPC or equivalent source of information is consulted before initiating the combination treatment with favipiravir.

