### **11.3 Consent**

Consent to enter the trial must be sought from each participant only after full explanation has been given, an information sheet offered and time allowed for consideration. Signed participant consent must be obtained, the consent forms should also be signed by the person carrying out the consent procedure at site, who must be detailed on the study specific delegation and training log as having authorisation. For patients who have capacity to understand and give consent, but are unable to read the consent form or sign their name, witness consent may be given. The PI is responsible for ensuring if the taking of consent is delegated to a designee, the designee is suitably qualified by training or experience to take informed consent.

The right of the participant to refuse to participate without giving reasons must be respected. After the participant has entered the trial the clinician remains free to give alternative treatment to that specified in the protocol at any stage if he/she feels it is in the best interests of the participant, but the reasons for doing so must be recorded. In these cases the participants remain within the trial for the purposes of follow-up and data analysis. All participants are free to withdraw at any time from the protocol treatment without giving reasons and without prejudicing further treatment.

An original completed consent form must be retained at each site in the appropriate section of the Investigator Site File, and a photocopy placed in the patient's medical records. All patients must be given either an original or a copy (as per local site practice) of the signed patient information sheet and consent form for their records. Consent forms must be retained on site and not submitted to the CRUK CTU Glasgow.

In the event that new patient information sheets/consent forms are produced throughout the duration of the trial, it may be that patients already participating in the trial should be re-consented to the updated version of the patient information sheet. However, if the principal investigator decides that this is not in the best interests of the patient re-consent is not required. Decisions not to re-consent patients must be documented in the patient's medical records.

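### Section 3.5.1 both keeps patients who stop treatment in follow-up and orders their removal from the trial; read literally, it could lose day-15 outcomes differentially by arm

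*Protocol*

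**What the plan says.** Section 3.5.1 is headed as dealing with withdrawal from trial treatment. It says in bold: "If a patient withdraws from treatment early, they should be followed up as per trial schedule". Directly below comes: "A subject must be discontinued from the trial for any of the following reasons". The reasons listed are withdrawal of consent, meeting the stopping rules (with a pointer to Section 6.8), investigator decision, a positive serum pregnancy test, "Noncompliance with trial treatment or procedure requirements", and administrative reasons.

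Other parts of the protocol bear on the same point:

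- **3.5.2** says it is often desirable that a patient who stops treatment stays on the trial, for example for follow-up. For a patient who does withdraw from the trial, "no further tissue will be collected or any other research procedures carried out on or in relation to the participant".
- **3.5.2** and **5.3.2** keep study assessments going for patients who lose capacity or can no longer swallow tablets.
- **5.8**, where the toxicity criteria actually stand, says "A subject should be removed from favipiravir treatment if one of the following criteria is met". It does not mention leaving the trial.
- **5.10.2** and the Duration paragraph of the Trial Summary follow every randomised participant to day 60 (the Summary adds: or death, if sooner).
- **11.3**, on patients switched to alternative treatment, says "In these cases the participants remain within the trial for the purposes of follow-up and data analysis".

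**The concern.** The two instructions in 3.5.1 cannot both be obeyed for a patient who meets a stopping rule or does not take the tablets, and the stronger verb is on the instruction to remove. A site that follows the list would end research procedures for that patient, because that is what 3.5.2 attaches to leaving the trial.

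Two of the listed grounds cannot occur in the control arm: the drug stopping rules and non-compliance with trial treatment. Dosing runs from day 1 to day 10, so removals on these grounds would mostly come before the day-15 primary assessment. The day-8, day-29 and day-60 scale values and survival would be exposed too. Loss that depends on arm and is related to outcome biases the randomised comparison, and no analysis can restore outcomes that were never collected.

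**Working it through.** **1. The passages side by side**

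| Situation | Text ending participation | Text continuing follow-up |
|---|---|---|
| Meets drug stopping criteria | 3.5.1 list | 3.5.1 bold sentence; 5.8 (off drug only); 5.10.2 |
| Does not take trial treatment | 3.5.1 list | 3.5.1 bold sentence; 3.5.2; 5.10.2 |
| Investigator decision | 3.5.1 list | 3.5.1 bold sentence; 5.10.2; 11.3 where the clinician changes treatment |
| Cannot swallow or loses capacity | not listed | 3.5.2; 5.3.2; 5.10.2 |

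Grounds possible only on favipiravir: stopping rules and treatment non-compliance. Grounds possible in either arm: procedure non-compliance, consent withdrawal, investigator decision, pregnancy and administrative reasons.

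**2. Does 302 contain room for loss?** Inputs from section 7.1: control percentages 11, 5, 7, 5, 13, 13, 12, 2, 16, 16; odds ratio 1.95; 90% power; 5% two-sided. The proportional-odds formula of Whitehead is

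N = 12(z₀.₉₇₅ + z₀.₉₀)² / [(ln OR)²(1 − Σp̄³)].

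Recomputing the experimental percentages at 1.95 gives Σp̄³ = 0.0222, and ln 1.95 = 0.6678. So N = 12 × 10.507 / (0.4460 × 0.9778) = 289.1 for a fixed design. Applying the section 7.2 boundaries at 128, 202 and 302 patients by simulation gives power 0.899 and, with futility stopping ignored, one-sided alpha 0.0251. The plan's 302 is therefore reproduced: the interim looks account for all of the increase over 289, and nothing is left for missing outcomes.

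**3. Power if outcomes are lost in the favipiravir arm only** (loss rates assumed): 89.2% at 5% lost, 88.3% at 10%, 87.4% at 15%, 86.3% at 20%. This effect is modest.

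**4. Bias under no true effect.** Assume 10% of the favipiravir arm is removed, the rest are analysed as complete cases, and removal is k times as frequent among patients who would be hospitalised or dead at day 15 (66% of the control distribution) as among the ambulatory (34%). With removal fractions r₁ and r₂:

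0.66 r₁ + 0.34 r₂ = 0.10 and r₁ = k r₂, so r₂ = 0.10 / (0.66k + 0.34).

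For k = 3: r₂ = 0.10/2.32 = 0.043 and r₁ = 0.129. The hospitalised-or-dead share among those remaining is 0.66 × 0.871/0.90 = 0.639, against 0.66 in controls. A proportional-odds fit to the two distributions gives ln OR = 0.0656. With 151 and 135.9 patients the square root of the information is 4.825, so the expected Z is 0.0656 × 4.825 = 0.317, and P(Z > 1.96) = P(standard normal > 1.643) = 0.050.

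| k | r₁ | r₂ | Remaining share hospitalised or dead | Complete-case OR | One-sided final-look error |
|---|---|---|---|---|---|
| 1/3 | 0.060 | 0.179 | 0.690 | 0.91 | 0.008 |
| 1 | 0.100 | 0.100 | 0.660 | 1.00 | 0.025 |
| 2 | 0.120 | 0.060 | 0.645 | 1.05 | 0.041 |
| 3 | 0.129 | 0.043 | 0.639 | 1.07 | 0.050 |
| 5 | 0.137 | 0.027 | 0.633 | 1.09 | 0.060 |

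An odds ratio above 1 favours favipiravir. At k = 3 the odds ratio is 1.03 with 5% removed and 1.11 with 15% removed.

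**The case against.** The strongest reply is that the offending phrase is a drafting slip. The list sits under a heading about treatment withdrawal, leaving the trial has its own section (3.5.2), the section number cited is wrong (5.8.2 makes the same error), and several passages say follow-up goes on. This stands to the extent that loss of outcomes is a risk from contradictory text, not a consequence the protocol settles. It does not remove the point. Sites must act on one of two instructions, the removal instruction is the one worded as mandatory, and its pointer does not lead to the text in 5.8 that would correct it.

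Four stronger readings are tempting, but the documents do not support them:

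- **That the bias must favour favipiravir.** The direction depends on k, for which the documents give no value. At k = 1 there is no bias; below 1 it reverses. The specific criteria in 5.8 are liver tests, uric acid and drug-attributed grade 3 or higher events, not COVID-19 severity.
- **That the rule removes patients too ill to take tablets.** Inability to swallow is not on the list, and 3.5.2 and 5.3.2 keep these patients under assessment.
- **That loss would fall almost only on the favipiravir arm.** This fits two grounds; the others can occur in either arm.
- **That toxicity after stopping would go unseen.** Section 6.1.2.2 follows adverse events to resolution or day 29, and 6.1.4 requires serious events to be reported to day 60, and later if thought related.

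**Conclusion.** The contradiction is certain: it is in the wording, within 3.5.1 and against 3.5.2, 5.3.2, 5.8, 5.10.2 and 11.3. So is the mechanism for arm-dependent loss, since two of the mandatory grounds can apply only to patients given trial drug.

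The size is not known. The removal rate, the ratio k and the complete-case analysis are all assumptions, so the table shows what the text could permit and is not a forecast. Within that range, removing 10% of one arm can move the one-sided error from 0.025 to anywhere between 0.008 and 0.060. The associated power loss is under two percentage points (89.9% to 88.3%). The possible bias is the reason to act, and it has to be prevented while outcomes are still being collected.

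**What to change.** Amend section 3.5.1 and the text that depends on it:

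1. Reword the lead-in to the list so that it requires discontinuation from trial treatment, not from the trial.
2. State that patients stopping treatment for a listed reason stay in outcome and safety follow-up to day 60, by telephone if they cannot attend.
3. Let data collection end early only when the patient withdraws consent for further data collection, and deal with that in 3.5.2 rather than in the treatment list.
4. Align the sentence in 3.5.2 about patients for whom continuing would be unsafe, so that it does not end outcome collection.
5. Correct the Section 6.8 references in 3.5.1 and 5.8.2 to 5.8.

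The cost is a short protocol amendment and a note to sites. The day-15, day-29 and day-60 assessments are already scheduled and section 4.2 already allows them by telephone, so no visits are added. The change concerns outcome collection only and leaves every drug-stopping criterion as it is.
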